**Methods:**

A total of 250 eligible participants will be equally assigned to 1 of 5 arms (healthy or subhealthy, prediabetes, diabetes, prediabetes with hypertension and dyslipidemia, and diabetes with hypertension and dyslipidemia). Participants aged 21-75 years, of any sex or race, and have been diagnosed with diabetes (fasting plasma glucose [FPG] of 7 mmol/L, or 2-hour plasma glucose [2hPG] of 11.1 mmol/L) or prediabetes (impaired FPG of 6.1-6.9 mmol/L, or impaired glucose tolerance with an 2hPG of 7.8-11 mmol/L) will be included. The Health Evaluation Questionnaire, Physical Activity Questionnaire, sugar intake assessment, Constitution in Chinese Medicine Questionnaire, radial pulse diagnosis, and tongue diagnosis will be performed in a single visit. ANOVA for continuous data and chi-square tests of independence will be used for categorical data assessments, with a level of *P*<.05 considered significant.

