### Specific Aims and Hypothesis

This study aims to identify the gap in syndrome differentiation between the subjective and objective TCM diagnosis. We devised a protocol for a nonrandomized, exploratory, observational case-control study with equal allocations in 5 arms to investigate the syndrome differentiation of diabetes and prediabetes. We hypothesize that the local TCM syndrome differentiation of diabetes and prediabetes in the tropical climate may differ from that defined based on the Chinese demographic. We also speculate that the high-frequency spectral energy (SE_13-50Hz_) may reflect a difference in pulse wave intensity and density between the healthy and diabetes groups. We will validate the syndrome differentiation using contemporary technologies such as the tongue imaging device and the pulse sphygmograph. An objective diagnosis of the tongue could be achieved with the advancement of artificial intelligence and imaging technology [36,37]. Images of the tongue captured with the tongue diagnostic device will then be processed through an algorithm for comparison and analysis against standard tongue diagnosis images (Figure 2). Furthermore, the development of pulse sphygmographs has enabled the digitalization of pulse assessment. Researchers investigated quantitative analyses of pulse profiles in the time and frequency domains [30]. The development of these quantitative and graphical representations of the pulse profiles in the 6-pulse positions is a significant step toward transforming traditional pulse diagnoses into scientific and objective assessments (Figure 1) [31].

The objective assessment will potentially increase the accuracy of the identification, diagnosis, and prevention of diabetes and prediabetes through a targeted treatment system tailored to the local population.

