#### The Constitution in Chinese Medicine Questionnaire

Based on TCM principles, the Chinese Medicine Questionnaire (CCMQ), which was established in 2009 by the China Association of Chinese Medicine, will be used to evaluate the body constitution of each participant. This questionnaire consists of 60 questions divided into nine categories of body constitution: (1) balanced, (2) qi deficiency, (3) yin deficiency, (4) yang deficiency, (5) phlegm dampness, (6) damp heat, (7) blood stasis, (8) qi stagnation, and (9) inherited special constitution. Each category has 7 or 8 questions. A 5-point Likert scale that quantitatively assesses the body characteristic is adopted, and the original score is obtained by summing the categorized items. The adjusted score is derived by: 100 [(original score – number of questions) / (number of questions 4)]. The scoring algorithm indicates the likelihood of a particular type of body constitution with a higher score. A subscale criterion of at least 30 points will be used to classify the body composition [41]. Table 4 provides the recommended assessing criteria [42].

Lu et al [41] concluded that the CCMQ is capable of measuring the 9 body constitutions with reasonably good construct validity and reliability. Another study reported that the reproducibility using the Spearman correlation coefficient for the subscales ranged from 0.76 to 0.90, indicating good repeatability and quantitativeness [43].

**Table 4 table4:** Assessing criteria of CCMQ^a^.

Adjusted score of balanced constitution	Total adjusted score of 8 unbalanced constitution	Body constitution
≥60	<30	Balanced constitution
≥60	30-39	Balanced constitution but leaning toward the unbalanced constitution with a score ≥40
≥60	≥40	Unbalanced constitution with a score ≥40
<60	≥40	Unbalanced constitution with the highest score
<60	30-39	Prone to an unbalanced constitution with the highest score

^a^CCMQ: Constitution in Chinese Medicine Questionnaire.

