#### Syndrome Differentiation

The syndrome differentiation of *xiao-ke* will be based on the objective assessment results analyzed from CCMQ, tongue, and pulse diagnosis regardless of the participants’ group status. Data collection under standardized conditions using contemporary diagnostic devices is expected to enhance stability and reliability in syndrome differentiation. This approach effectively minimizes bias and eliminates the necessity for blinding in our study design.

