### Statistical Analyses

The baseline variables (age, sex, height, body weight, BMI, and blood sugar levels), MET-minutes for physical activity, scoring of body constitution, pulse assessments, and tongue analysis results will be compared between the five groups.

Using ANOVA, we will compare the variances across the means of the SE_13-50 Hz_ value from the pulse sphygmograph between each group and the control. Analysis of covariance will also be used to assess the group differences while controlling for potential confounding variables such as gender, age, BMI, physical activity levels, and others. Using the Bonferroni test for post hoc multiple comparisons, the mean values will be compared and corrected. Chi-square tests will also be used to do the comparative analysis of the body constitutions or syndromes between the objective and subjective assessments. All tests will be 2-tailed and *P*<.05 will be considered statistically significant. We will use STATA (standard edition version 18.0; StataCorp LLC) for the analysis.

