### Conclusions

To the best of our knowledge, this is the first study to use contemporary TCM diagnostic instruments to map expert and empirical knowledge of TCM to its scientific equivalents for the purpose of evaluating the syndrome differentiation of diabetes. In addition to identifying the pulse wave and tongue morphology, both devices are also capable of distinguishing the TCM body constitution and syndrome differentiation through the processing of the identified characteristics by their artificial intelligence algorithm. We will compare and contrast the outcomes of the digital analysis and the CCMQ.

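### Chi-square tests of independence are assigned to the objective-versus-subjective comparison, but the two ratings come from the same people and the test measures neither their agreement nor the gap between them

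*Protocol article*

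**What the plan says.** All places are in the protocol article.

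- **Aim** (Specific Aims and Hypothesis): "This study aims to identify the gap in syndrome differentiation between the subjective and objective TCM diagnosis".
- **Method for that comparison** (Statistical Analyses): "Chi-square tests will also be used to do the comparative analysis of the body constitutions or syndromes between the objective and subjective assessments".
- **Kind of chi-square** (abstract, Methods): "chi-square tests of independence will be used for categorical data assessments".
- **Same people, same visit.** The abstract says that the questionnaires, "radial pulse diagnosis, and tongue diagnosis will be performed in a single visit". The CCMQ section says the questionnaire "will be used to evaluate the body constitution of each participant". Table 3 schedules the questionnaires and both device assessments for everyone.
- **Which ratings are set against each other** (Conclusions): "We will compare and contrast the outcomes of the digital analysis and the CCMQ".
- **Where the CCMQ is classed** (Syndrome Differentiation): the syndrome "will be based on the objective assessment results analyzed from CCMQ, tongue, and pulse diagnosis". Here the CCMQ is an objective input. In the Conclusions it is the comparator to the digital output.
- **Reconciliation** (Tongue Diagnosis): the tongue system's result is to be reconciled with the pulse diagnosis and the CCMQ.

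**The concern.** Each participant contributes a CCMQ constitution and a device-reported constitution. The aim asks how far the two differ. A chi-square test of independence can be applied to such data in two ways, and neither answers that question.

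1. **Cross-table of one rating against the other.** The null hypothesis is that the ratings are unrelated. Rejecting it says only that they are associated, which is compatible with poor agreement and even with systematic disagreement.
2. **Table of method by category.** Each person is counted twice as if two people had been sampled. Only the marginal frequencies enter, so disagreement within a person is invisible, and the standard error is wrong because the pairing is ignored.

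The Discussion expects the study to help establish the reliability of the devices for wider clinical use. A small P value from the first table could be reported as support for the devices when agreement is poor. A large P value from the second could be reported as showing no gap when the methods disagree on many people.

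**Working it through.** **Inputs from the document:** 250 participants, 5 x 50; two-tailed P<.05; nine CCMQ constitutions. The document gives no expected cross-table, category frequencies or kappa, so there is no stated figure to reproduce for this comparison. All tables and distributions below are assumptions for illustration.

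**Step 1. Association is not agreement (cross-table).** For a 2x2 table with cells a, b, c, d (a and d are agreements), chi-square = N x phi^2, with phi = (ad - bc) / sqrt(product of the four margins). Kappa = (po - pe)/(1 - pe), where po is the observed agreement and pe the agreement expected by chance.

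| | a, b, c, d | Agreement | phi | Chi-square | Kappa |
|---|---|---|---|---|---|
| Table A | 110, 15, 15, 110 | 220/250 = 88% | (12100 - 225)/15625 = 0.76 | 250 x 0.5776 = 144.4 | (0.88 - 0.5)/0.5 = 0.76 |
| Table B | 15, 110, 110, 15 | 30/250 = 12% | (225 - 12100)/15625 = -0.76 | 250 x 0.5776 = 144.4 | (0.12 - 0.5)/0.5 = -0.76 |

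The test returns the same value for opposite findings.

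**Step 2. How weak can agreement be and still give P<.05?** Assume nine constitutions with frequencies 20, 20, 15, 15, 8, 8, 6, 5 and 3%, the same for both methods. With probability kappa the second rating copies the first; otherwise it is drawn independently. The noncentrality is then N x kappa^2 x (9 - 1), with 8 x 8 = 64 degrees of freedom and a critical value of 83.7.

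- Kappa 0.1: 250 x 0.01 x 8 = 20. Rejection is about 49% by the noncentral chi-square approximation and about 53% by simulation.
- Kappa 0.2: 250 x 0.04 x 8 = 80. Rejection is above 99% by the approximation and 99% by simulation.

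**Step 3. Method-by-category table.** Tables A and B both have margins of 125/125 for each method, so this test gives chi-square 0 and P=1 for both.

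Now take Table C with cells 100, 25, 5, 120. Method 1 assigns the category to 125/250 = 50% and method 2 to 105/250 = 42%. Agreement is 88% and kappa 0.76.

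- Unpaired chi-square: pooled proportion 230/500 = 0.46; 0.08^2 / (0.46 x 0.54 x 2/250) = 0.0064/0.001987 = 3.22, P=.073.
- McNemar: (25 - 5)^2 / (25 + 5) = 400/30 = 13.33, P=.0003.

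**Step 4. Why the unpaired test is conservative.** With equal margins and within-person correlation phi, the variance of the difference is smaller by the factor (1 - phi) than the test assumes. The true size at nominal 0.05 is 2 x [1 - Phi(1.96/sqrt(1 - phi))]: 0.019 at phi 0.3, 0.006 at 0.5 and 0.0003 at 0.7. At N=250, for 50% against 40%, power is 0.64 unpaired and 0.76 with McNemar at phi 0.3, and 0.66 and 0.88 at phi 0.5.

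**The case against.** **The article is condensed and no SAP is shown.** Agreement statistics may be planned there, so a reader should not infer that the size of the gap will never be estimated; the document does not show that. What stands is narrower: the article does not leave the method open. It names a test, and the abstract's wording weighs against reading it as McNemar's chi-square.

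**The tables may seem too sparse for chi-square in general.** This is not supported. In the method-by-category table at N=250, under the Step 2 frequencies, the smallest expected count is 250 x 0.03 = 7.5. In the 9x9 cross-table, 65 of 81 expected counts are below 5, yet the simulated type I error at N=250 is about 4 to 5%. The objection to the test is the question it asks.

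**The margin test's low rejection rate may seem a failure in itself.** With equal margins there is no shift to find, so rejecting in 5% of studies or fewer is what any valid margin test would do. The fault is lost power when there is a shift, and blindness to disagreement within a person.

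**It is unclear what the subjective rating is.** This stands. Table 3 lists no practitioner pulse or tongue diagnosis, and the CCMQ is classed as objective in one section and set against the devices in another. If it feeds the composite and is also the comparator, agreement is inflated. Kappa therefore cannot simply be substituted into the existing sentence.

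**The study is exploratory and names no primary endpoint, and its sample size rests on pulse-wave studies.** True, and it limits the consequences. But the comparison is the first aim stated, and the named test cannot answer it.

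**Conclusion.** The concern holds for the objective-versus-subjective comparison only. The test named for a stated aim does not measure agreement and does not validly test a marginal gap between paired ratings.

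The main conclusion needs no assumed distribution: identical chi-square values for 88% and 12% agreement follow from the form of the statistic. The rejection rates (about 53% at kappa 0.1 and 99% at 0.2) rest on the assumed nine-category frequencies, equal margins and N=250. The P=.073 against P=.0003 contrast is one illustrative table. If syndromes are compared instead, Table 2 lists five, and the rates would differ.

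Chi-square remains suitable for comparing constitution or syndrome frequencies between the five independent groups.

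**What to change.** Replace the sentence in Statistical Analyses, in this order.

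1. **Name the two ratings** and reconcile the Syndrome Differentiation section with the Conclusions. Use the CCMQ constitution against the device-reported constitution, recorded before the reconciliation described under Tongue Diagnosis, so that the CCMQ is on one side only. State the common category scale, including how the intermediate classes of Table 4 are handled. If both devices report a constitution, make one comparison for each.
2. **Estimate agreement:** percent agreement and Cohen's kappa with a 95% CI, by group and overall, plus category-specific agreement. The by-group results matter because the groups are filled by quota, so the overall figure depends on an artificial mix.
3. **Test marginal shift** with McNemar for one category or Stuart-Maxwell for several.
4. **Keep chi-square or exact tests** for comparisons between the five groups.

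The planned numbers give usable precision. Under the Step 2 frequencies pe = 0.145, so at kappa 0.4 po = 0.487 and SE is about sqrt(po(1 - po)/n)/(1 - pe). That is 0.037 at n=250 (95% CI about ±0.07) and 0.083 at n=50 (about ±0.16).

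The cost is a change of analysis wording. Not all data are in hand, since the article reports 140 enrolled of 250, so the change can be made before analysis while enrolment continues. The planned visit already yields both the CCMQ and the device ratings. The one practical condition is that the device output is kept as reported, before reconciliation.

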### Sample Size Calculation

In an earlier 3-arm study to investigate the relationship between dyspepsia and rhinitis conducted by Huang et al [44] with 42 participants assigned to each group, there was a significant difference in the high-frequency pulse SE (SE_13-50Hz_) between the control and experimental groups. Huang et al [45] also compared the radial pulse wave characteristics of hypertensive patients against healthy individuals with 46 patients in each group using the same device. Other investigations using the pulse tonometric device indicated a sample size of 25 with an expectation of 5% type 1 error, 80% power, and 5% drop rates based on the mean and SD derived from a study conducted by Huang et al [46,47]. Although there is limited prior data on the investigation of syndrome differentiation and pulse diagnosis of diabetes and prediabetes, we anticipate that a sample size of 50 in each group will provide adequate power to detect statistical significance.

### Retention of Trial Documents

In a secure storage facility, the principal investigator will maintain all source documentation (including evidence of research eligibility, history and physical findings, and diagnostic test results), as well as ethical review records and other regulatory documentation. The documents should be available for inspection and duplication by authorized parties. The study coordinator will ensure that all documentation is current and up to date.

## Results

Recruitment has been in progress since September 2022.

## Discussion

### Expected Findings

We anticipate that diabetes and prediabetes with or without hypertension and dyslipidemia would have different body constitutions compared to healthy individuals. The prevalence of specific TCM syndrome differentiation may be more common in countries with hot and humid tropical climates, albeit it may differ from the Chinese demographic.

TCM diagnosis is a comprehensive approach that integrates observation, inquiry, pulse palpation, and tongue diagnosis. Finger sensitivity required for palpating radial pulses and precise visual assessment of the tongue are fundamental to accurately detecting variations in the pulse and tongue quality in TCM diagnosis. However, traditional methods of syndrome differentiation are highly subjective and skill dependent. The interpretation of pulse quality and tongue characteristics can differ across practitioners based on their clinical training, experience, and personal bias. This may result in observations lacking clinical significance. To mitigate subjectivity and provide impartial evaluations, we designed this protocol to examine the syndrome differentiation of patients with diabetes and those with prediabetes using contemporary TCM diagnostic technologies. The data collected and evaluated under standardized conditions using these contemporary diagnostic devices are expected to yield stable and unbiased results. This standardized assessment will facilitate more consistent and reliable syndrome differentiation, which is crucial for both clinical practice and research. Thus, our findings may enhance the accuracy of the identification, diagnosis, treatment, and prevention of diabetes and prediabetes through targeted approaches, potentially improving patient outcomes and management effectiveness. Additionally, we will explore and analyze the correlation between TCM syndrome differentiation and WHO diagnosis criteria for diabetes. Establishing the reliability of contemporary TCM diagnostic tools sets the stage for their broader adoption in clinical practice and enables future research into individualized treatment plans based on objective TCM syndrome differentiation. Some of the following study challenges are expected.

#### Sufficient Sample Size

Estimating the sample size for a TCM study, especially when using diagnostic devices investigating syndrome differentiation and pulse diagnosis, can be indeed challenging. There is currently limited preexisting data specifically focusing on the syndrome differentiation and pulse diagnosis in the context of our study. Since this study is a pilot investigation into the TCM syndromes in patients with diabetes and those with prediabetes using digital diagnostic instruments, we used prior studies conducted by Huang et al [44,45] as a reference to estimate the required sample size. These studies used the older model of pulse sphygmograph to investigate the pulse characteristics of chronic conditions such as hypertension, dyspepsia, and rhinitis as well as healthy individuals.

#### Recruiting Eligible Participants

The recruitment of eligible participants is undoubtedly the most crucial, challenging, and unpredictable component of clinical research. Aside from the main strategies such as physician referral, recruitment posters, and social media, publicity can also be disseminated through newspapers, health magazines, or health education to promote awareness and public interest, following the necessary ethical approval. Furthermore, a lack of sufficient knowledge about the study process or clinical trial benefits can be one of the primary barriers to research recruitment. To overcome this barrier, we ensure to provide good communication to the physicians and participants through the designs of advertising posters, health studies, and informed consent. In addition, we reduce the study burden by providing flexibility and accommodation on research visits.

### Conclusions

To the best of our knowledge, this is the first study to use contemporary TCM diagnostic instruments to map expert and empirical knowledge of TCM to its scientific equivalents for the purpose of evaluating the syndrome differentiation of diabetes. In addition to identifying the pulse wave and tongue morphology, both devices are also capable of distinguishing the TCM body constitution and syndrome differentiation through the processing of the identified characteristics by their artificial intelligence algorithm. We will compare and contrast the outcomes of the digital analysis and the CCMQ.

## Abbreviations

2hPG: 2-hour plasma glucose
CCMQ: Constitution in Chinese Medicine Questionnaire
FPG: fasting plasma glucose
HbA1c: glycated hemoglobin A1c
MET: metabolic equivalent task
PIEC: Parkway Independent Ethics Committee
SE: spectral energy
TCM: traditional Chinese medicine
WHO: World Health Organization
